### Safety surveillance

During both phases of the trial, safety surveillance includes monitoring of 1) AEs/TEAEs/SAEs summarized by grade, attribution, and body systems, by number of events, and by participant, 2) physical exam abnormalities, 3) vital signs (weight, blood pressure, pulse rate, temperature, respiration rate), 4) standard 12-lead resting ECG measures, and 4) summaries of safety laboratory tests.

### Outcomes

#### Phase 2A primary endpoints

The primary safety endpoint in phase 2A is the rate of TEs in active and placebo arms at each dose. A TE is defined as early discontinuation of the IP due to intolerability or a post-randomization moderate or severe AE that is possibly, probably or definitely related to the IP.

#### Phase 2A secondary endpoints

Secondary safety and tolerability endpoints for phase 2A include: 1) number of participants with AEs/TEAEs and SAEs, 2) number of participant withdrawals from the study, and 3) number of participants discontinuing IP.

#### Phase 2B primary endpoints

The primary cognitive endpoint is the within-participant change from baseline to 72 weeks compared between active arm and placebo on the ADAS-Cog13 [23,24]. The primary functional endpoint is the within-participant change from baseline to 72 weeks compared between active arm and placebo on the CDR-Sum of Boxes (SB) [25,26].

#### Phase 2B secondary safety and tolerability endpoints

Secondary safety and tolerability endpoints for phase 2B include: 1) number of participants with AEs/TEAEs and SAEs 2) number of participant withdrawals from the study, and 3) number of participants discontinuing IP.

#### Phase 2B secondary PK endpoints

Secondary PK endpoints for phase 2B include mean and median levels of: 1) thiamine (nmol/L), 2) thiamine diphosphate (ThDP) (nmol/L), 3) thiamine monophosphate (ThMP) (nmol/L) [27], and 4) erythrocyte transketolase activity (U/g haemoglobin (U/gHb)) [28,29]. Measures of ThDP, ThMP, and erythrocyte transketolase activity will be provided as blood markers of efficacy of drug delivery. These measurements will be conducted on whole and red blood cells in samples collected at baseline, week 8, and week 72.

#### Phase 2B secondary efficacy endpoints

Additional efficacy endpoints of benfotiamine will be assessed by within-participant change from baseline to week 72 between active arm and placebo on the following: 1) the Alzheimer’s Disease Cooperative Study–Activities of Daily Living Scale for use in Mild Cognitive Impairment (ADCS-ADL-MCI) [30] to evaluate preservation or potential improvement in everyday activities of daily living, and 2) the MoCA [31] to evaluate preservation or potential improvement in cognitive function.

#### Phase 2B exploratory endpoints

Exploratory endpoints in phase 2B include within-participant longitudinal change between active arm and placebo in: 1) cranial MRI volumetric measures of hippocampal, whole brain, and ventricles, as well as regional cortical thickness, 2) scores on the Neuropsychiatric Inventory (NPI) [32], 3) scores on neuropsychological test measures administered remotely and in-person, 4) ADAS-Cog-Exec [33] scores, 5) levels of plasma biomarkers Aβ42/Aβ40 ratio, p-tau217/np-tau217 ratio, p-tau217, total tau, p-tau 231, NfL and GFAP, 6) AGE levels measured in plasma as an exploratory endpoint of PD, and 7) PK (plasma thiamine, thiamine esters in whole blood including ThDP and ThMP, and erythrocyte transketolase activity) relationships to PD biomarkers (AGE) and clinical outcome measures.

AGE levels will be measured on plasma samples and four AGE by mass spectrometry (N(6)-carboxymethyl-lysine (CML), pentosidine, N(6)-carboxymethyl-lysine (CEL), methylglyoxal-derived hydroimidazolone) will be quantified to measure all specific modes of action of benfotiamine.

Neuropsychological measures administered in-person include the Boston Naming Test (30-item) [34], the Trail Making Test (Parts A and B) [35], and WAIS-R Digit Symbol Substitution [36]. Neuropsychological measures administered remotely (via video-call) include Immediate and Delayed Recall from the Rey Auditory Verbal Learning Test [37], Number Span Forward and Backward [38], Category Fluency [39] and Letter Fluency [39]. Remote measures will be administered over videoconference-call within 10 days after each in-person visit (baseline, week 24, week 48, and week 72). Participants will use their own interactive video capable devices for the remote assessments, although study-provided devices will be available, as needed.

### Power calculation and sample size

Table 3 shows that with a total sample size of n = 406 (203/arm), a 20% dropout rate, and a 5% drop-in rate from the placebo arm to active treatment, the trial will be powered at 80% overall (90% on each endpoint separately) to detect a difference between arms, corresponding to a Cohen’s d effect size of 0.38 which represents a small to moderate effect size. This would be a reasonable and clinically relevant difference between arms on each co-primary endpoint, and would be commensurate to the 35% to 40% amelioration of decline seen in the placebo arm of the recently completed phase 2 trial of donanemab in patients with early AD [40], and would correspond to an absolute difference between arms on the CDR-SB of 0.7 points (assumed SD = 1.74) and of 1.7 points (assumed SD = 4.35) on the ADAS-Cog13.

**Table 3 pone.0302998.t003:** Sample sizes which achieve 90% power for given effect sizes (Cohen’s D; difference between the 2 arms), assuming 20% dropout and assuming drop-in rates of 5% and 10%.

drop-in rate	effect size	n / arm
5%	0.35	239
**5%**	**0.38**	**203**
5%	0.40	183
10%	0.35	266
10%	0.38	226
10%	0.40	204

### Statistical analyses

#### Phase 2A

When criteria have been reached to end phase 2A, the unblinded safety biostatistician will alert the PIs ([name], [name], [name]) that the database is to be frozen. An unblinded safety report will be provided to the Data Safety Monitoring Board (DSMB). The phase 2A primary analysis will compare the rate of TEs between the 1200 mg/d arm and the placebo arm. The analysis will test whether the rate of TEs is unacceptably high in this high-dose arm compared to placebo, using a formal one-sided hypothesis test of equal rates, against the one-sided alternative that the high dose arm TE rate is greater than the placebo arm TE rate. The conditional one-sided test of Przyborowski and Wilenski [41] will be used, at 5% significance level.

Additional phase 2A safety analyses will involve computing an exact upper-one sided 95% confidence interval for the TE rate in each arm. Safety and tolerability data and demographic data will be summarized in a tabular and/or graphical format for each treatment group. The incidence of all laboratory test abnormalities and median changes from baseline will be tabulated by treatment regimen and time point. The safety population (i.e., enrolled and randomized participants who received at least 1 dose of blinded study therapy) will be used for these analyses.

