**Methods:**

This is the protocol for a randomized, double-blind, placebo-controlled 72-week clinical trial of benfotiamine in 406 participants with early AD. Phase 2A determines the highest safe and well-tolerated dose of benfotiamine to be carried forward to phase 2B. During phase 2A, real-time monitoring of pre-defined safety stopping criteria in the first approximately 150 enrollees will help determine which dose (600 mg or 1200 mg) will be carried forward into phase 2B. The phase 2A primary analysis will test whether the rate of tolerability events (TEs) is unacceptably high in the high-dose arm compared to placebo. The primary safety endpoint in phase 2A is the rate of TEs compared between active and placebo arms, at each dose. The completion of phase 2A will seamlessly transition to phase 2B without pausing or stopping the trial. Phase 2B will assess efficacy and longer-term safety of benfotiamine in a larger group of participants through 72 weeks of treatment, at the selected dose. The co-primary efficacy endpoints in phase 2B are CDR-Sum of Boxes and ADAS-Cog13. Secondary endpoints include safety and tolerability measures; pharmacokinetic measures of thiamine and its esters, erythrocyte transketolase activity as blood markers of efficacy of drug delivery; ADCS-ADL-MCI; and MoCA.

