### Design

This overall design is a placebo controlled parallel group RCT over 72 weeks. The Phase 2A safety and dose selection decision will be reached when either 21 total TEs have been observed across both the high dose arm and the placebo arm, or when 160 person-months of exposure have accumulated in each of the high dose and placebo arms, whichever comes first (see S1 File). If the tolerability stopping rule is not reached by this predetermined number of TEs, the 1200 mg dose will continue, the 600 mg dose will be titrated upwards, and randomization will be adjusted for the remainder of trial enrollment to be 1:1 active versus placebo across the trial population. The completion of phase 2A will seamlessly transition to phase 2B without pausing or stopping the trial. Phase 2B will assess efficacy and longer-term safety of benfotiamine at the selected dose in a larger group of participants through 72 weeks of treatment.

The schedule of enrollment, interventions, and assessments is shown in Fig 1. The study schematic is shown in Fig 2.

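### Not rejecting equal TE rates does not bound the excess on 1200 mg/d: the phase 2A report needs an upper limit for the rate ratio at each dose, and the abstract and analysis section need reconciling on 600 mg/d

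*Protocol article*

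**What the plan says.** The abstract gives the purpose of the first stage: "Phase 2A determines the highest safe and well-tolerated dose of benfotiamine to be carried forward to phase 2B". The Objectives section makes this the primary objective of phase 2A, judged by the TE rate.

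The Phase 2A analysis section supplies the test: "using a formal one-sided hypothesis test of equal rates, against the one-sided alternative that the high dose arm TE rate is greater". Placebo is the comparator. On the method the section adds: "The conditional one-sided test of Przyborowski and Wilenski [41] will be used, at 5% significance level". Its purpose is stated as "The analysis will test whether the rate of TEs is unacceptably high in this high-dose arm compared to placebo". No margin or rate ratio that would count as unacceptable is named.

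The Design section gives two ways for phase 2A to end. One is an event count: "when either 21 total TEs have been observed across both the high dose arm and the placebo arm". The other, if it happens sooner, is a total exposure of 160 person-months in both of those arms. If the tolerability stopping rule has not been reached, 1200 mg/d continues and the 600 mg/d arm moves up to it. The section refers to S1 File for detail.

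On the endpoint, the Phase 2A primary endpoints section reads: "The primary safety endpoint in phase 2A is the rate of TEs in active and placebo arms at each dose". The abstract goes further and describes active and placebo TE rates as being compared, dose by dose. The analysis section formally compares only 1200 mg/d with placebo. Each arm, including 600 mg/d, also receives an exact one-sided upper 95% limit for its own TE rate. The DSMB section gives the DSMB the final dose recommendation, and the Phase 2A section says that it receives an unblinded safety report.

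**The concern.** The direction of the test and the direction of the conclusion differ. With equal rates as the null, the burden is on the data to prove an excess; where they cannot, the default is to carry 1200 mg/d forward. With at most 21 events, non-rejection is compatible with a large true excess. A conclusion that the dose is well tolerated needs an upper bound on the excess over placebo, and nothing planned supplies one. Separate upper limits for each arm's rate do not bound the ratio or the difference between arms.

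At stake is what the DSMB has before it when it recommends the phase 2B dose, since all phase 2A active-arm participants then move to that dose, and how the phase 2A result is later described. Separately, a reader of the abstract expects a 600 mg/d v placebo comparison that the analysis section does not contain.

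**Working it through.** **Inputs from the article.** One-sided 5% conditional test of two Poisson rates, 1200 mg/d v placebo (Phase 2A analysis section); a maximum of 21 TEs in the two arms together, or 160 person-months in each (Design); 1:1:1 allocation, hence 1:1 for these two arms (Randomization and blinding).

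**Assumptions.** Equal exposure in the two arms, independent TEs, one test at the end of phase 2A. The article gives no target rate ratio and no placebo TE rate, so ranges are shown. It states no power for phase 2A, so there is no stated figure to reproduce.

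**1. Rejection boundary.** Given n TEs in total and equal exposure, the number X in the 1200 mg/d arm is Binomial(n, RR/(1+RR)), with success probability 0.5 under the null. For n = 21:
- P(X ≥ 14 | 0.5) = 0.095, above 0.05.
- P(X ≥ 15 | 0.5) = 0.039, so rejection needs 15 v 6 or worse, and the true size is 3.9%.

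**2. Power at 21 TEs.** Power = P(X ≥ 15 | 21, RR/(1+RR)).

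| Assumed rate ratio | RR/(1+RR) | Power |
|---|---|---|
| 1.5 | 0.600 | 20% |
| 2 | 0.667 | 42% |
| 2.5 | 0.714 | 61% |
| 3 | 0.750 | 74% |
| 4 | 0.800 | 89% |

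Power reaches 80% at a ratio of about 3.3. No total below 21 gives more than 42% at ratio 2; the next best is 41% at 18 TEs.

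**3. What a non-rejection leaves open.** The exact (Clopper-Pearson) one-sided 95% upper limit for the share of TEs in the 1200 mg/d arm, p_U, converts to a rate ratio by p_U/(1 − p_U).
- 14 v 7 (observed ratio 2, not rejected): p_U = 0.832, so 0.832/0.168 = 4.9.
- 11 v 10 (nearly equal): p_U = 0.714, so 0.714/0.286 = 2.5.

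**4. If the exposure limit comes first.** With placebo rate λ per person-month, the expected placebo count is 160λ, and the total is Poisson with mean 160λ(1 + RR), truncated at 21. Averaging the conditional power over that total:

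| Assumed λ | Expected placebo TEs | Power at RR 2 | Power at RR 3 |
|---|---|---|---|
| 0.02 | 3.2 | 16% | 46% |
| 0.025 | 4 | 22% | 57% |
| 0.0375 | 6 | 33% | 71% |
| 0.05 | 8 | 40% | 74% |

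With 10 TEs, 8 v 2 does not reject (p = 0.055). With four or fewer, rejection is impossible, since 4 v 0 gives p = 0.0625.

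**5. Sensitivity to repeated looks.** Applying the nominal 5% test after every TE up to 21 gives 54% power at ratio 2 and 82% at 3, but an overall size of 10.5%. Constant nominal levels with an overall size near 5% (4.8% to 5.7%) give about 36% to 40% at ratio 2.

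**6. The 600 mg/d comparison, side by side.** The abstract has TE rates compared with placebo at each dose. The endpoint section has TE rates at each dose, without the word compared. The analysis section has a test of 1200 mg/d v placebo, and for 600 mg/d its own rate with an upper limit plus tabulations. The endpoint section fits the analysis; the abstract does not.

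**The case against.** Four points can be made for the plan.

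- **The rule may be sequential.** The abstract describes real-time monitoring of predefined stopping criteria, and the Design section refers to S1 File. A reader might infer that 42% is the most power the plan can have against a doubled rate. The article does not support that: the figure belongs to a single final test, and step 5 shows that an uncorrected look after each TE would give more, at an inflated overall size. This stands, and the power figures must be read with it.
- **The ratio of 2 is not the plan's.** The article names no ratio, and power is 74% at 3 and 89% at 4. This stands, so the whole range is shown. Nor is the absence of a stated phase 2A power a fault in itself, since an article may leave that to the full protocol or supplement.
- **Non-rejection is not the only safeguard.** A reader might infer that the plan takes non-rejection as proof of tolerability. It does not say so: the DSMB decides from an unblinded report with per-arm limits, meets quarterly and can recommend halting. A one-sided test for harm is a common safety rule. This stands, but the DSMB's role makes a bound on the excess more useful, and per-arm limits do not give one.
- **600 mg/d is described, and the dose rule turns on 1200 mg/d.** This stands too. It would be too strong to say that the endpoint section declares a comparison that is then dropped, because that section declares rates only. The mismatch lies between the abstract and the analysis section.

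**Conclusion.** The point holds as an improvement to reporting and wording; it does not show that the dose rule is invalid. The equal-rates test is the default route by which 1200 mg/d goes forward, the aim is worded as determining a safe and well-tolerated dose, and no planned quantity bounds the excess over placebo. At the maximum of 21 TEs, an observed doubling passes with ratios up to 4.9 not excluded, and even a near-equal split leaves ratios up to 2.5 open. These limits assume equal exposure and independent TEs; repeat TEs in one participant would make them less reliable. The power figures (42% at ratio 2, 74% at 3) also assume one final look and depend on a ratio that the article does not give. S1 File could change them, but it would not turn a non-rejection into a bound. The difference between the abstract and the analysis section on 600 mg/d needs no assumption.

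**What to change.** 1. In the unblinded phase 2A report to the DSMB, add the exact one-sided 95% upper confidence limit for the TE rate ratio, once for 1200 mg/d v placebo and once for 600 mg/d v placebo.
2. Word a non-rejection as: an excess over placebo was not shown, and rate ratios up to X are not excluded, with X the reported limit.
3. Reconcile the abstract with the Phase 2A analysis section on whether 600 mg/d is compared with placebo. The second limit in item 1 would supply that comparison.

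The decision threshold and the choice of dose remain with the DSMB and the clinical team. The cost is two extra lines in a report already planned and a less favourable wording of the phase 2A conclusion. With so few events the limits will often be wide, which is the information the DSMB should have. No participant, visit or test is added.

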#### Phase 2B

The primary analyses will be performed on the modified intent to treat (mITT) population which includes all randomized participants who took at least one dose of the study medication, have a baseline assessment of the co-primary efficacy endpoints, and have at least one efficacy evaluation following baseline. The primary analysis will be the same for each co-primary endpoint (CDR-SB and ADAS-Cog13) and will test within subject change in the measure as the outcome in a mixed effects repeated measures model using all available outcomes in the mITT population with no imputation for missing data. Fixed effects in the model will be *APOE* status, baseline value of the outcome measure, baseline by visit-week interaction term, treatment group, visit-week, and visit-week by treatment group interaction. The approach will be maximum likelihood. Visit will be treated as a categorical variable. The covariance structure will be specified as follows: the random effects will include site and subject. The within-subject covariance will be unstructured. If needed, sites will be pooled (in order of enrollment, starting from minimum enrollment) so that there is a minimum of 5 participants per site. If the model fails to converge at the default setting for the software used, then site will be changed to a fixed effect, and if this model does not converge, site will be removed from the model. If the model does not converge, the following structures for the within subject covariance will be fit, sequentially, until the structure is found that results in convergence of the model: Huynh-Feldt, Toeplitz, Autoregressive (1), and Compound Symmetry. A sandwich estimator will be utilized to estimate the variance estimates, and degrees of freedom will be calculated using the between-within method. The primary endpoint will be tested using model-adjusted least squares means at the week 72 visit. Point estimates, standard errors, two-sided 95% confidence intervals, and p-values will be presented.

Mean changes in the secondary endpoints from baseline to week 72 will be compared between arms using the analysis strategy outlined above. To control alpha over the primary and all secondary endpoints, an overall hierarchical gatekeeper strategy will be used, similar to the primary analysis. First, if the primary analysis is not significant, then the secondary endpoints will not be formally tested, and will be presented using exploratory summary statistics only (means and uncorrected 95% confidence intervals by arm and for the difference between arms).

No claims of statistical significance will be made. However, if the primary analysis is significant, the secondary endpoints will be tested in the listed order in hierarchical manner, each using an alpha of 5%. Once a secondary endpoint has failed to attain the prespecified 5% significance level, the remaining secondary endpoints will be presented as exploratory only. This strategy will maintain the overall familywise significance level for the primary and all secondary endpoints at 5%. Exploratory analyses will be detailed in the statistical analysis plan, and will generally be similar to the primary and secondary analyses.

Safety and tolerability data as well as demographic data for the safety population will be summarized in tabular and/or graphical format for each treatment group. The incidence of all laboratory test abnormalities and the median changes from baseline will be tabulated by treatment regimen and time point.

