### Concomitant medications

Use of the following medications is prohibited throughout participation in the study: thiamine or benfotiamine supplements outside of a multivitamin, immunosuppressive medications, chemotherapeutic agents for malignancy, or any concomitant treatment which may impair cognitive function. Medications that are central nervous system active (e.g., hypnotics) and may affect cognitive function are not permitted for 72 hours prior to neuropsychological testing.

Eligible participants being treated with FDA-approved acetylcholinesterase inhibitors (AchEI) and/or memantine at the time of screening are expected to remain on a stable dosage regimen of these medications for the duration of the trial. They may be initiated as clinically indicated during the study when a participant is not already on these medications at the outset, with appropriate documentation. FDA-approved monoclonal antibodies targeting brain amyloid are permitted, but participants must be stable for at least 6 months on such treatment prior to screening. For medications not intended to treat AD, participants must be on a stable dose for at least 4 weeks prior to baseline, except for medications which are administered for a short course of treatment.

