### Randomization and blinding

A randomization schedule will be generated and incorporated into an electronic Randomization and Trial Supplies Management (RTSM) system. The treatment group will be assigned as the site randomizes the participant. In phase 2A of the trial, as shown in Fig 2, each participant will be randomly allocated in a 1:1:1 ratio into one of the 3 groups: 1200 mg/d benfotiamine, 600 mg/d benfotiamine or placebo. At the dose decision point that ends phase 2A, all participants enrolled in the two phase 2A active dose arms will receive a new supply of benfotiamine at the selected highest tolerable dose for phase 2B. An unscheduled visit at the start of phase 2B may be required to replace IP supply in all active participants once the phase 2A dose selection is made. Newly enrolled participants will be randomized 1:2 active arm to placebo arm until parity is achieved between numbers of active and placebo arm participants (approximately 150 participants total), randomized 1:1 thereafter (approximately 100 participants). In both phases of the trial, the randomization will be stratified by site.

Participants and study personnel will be blinded to both treatment arm and dosage. There will be provisions for the site Principal Investigator (PI) to unblind treatment assignment in consultation with the ADCS Medical Monitor only in the case of an emergency.

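### The primary model has no term for baseline anti-amyloid antibody use and holds the APOE effect constant across visits; a low-cost gain in precision and in protection against drift, not an error

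*Protocol article*

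**What the plan says.** Protocol article, Statistical analyses, Phase 2B: the fixed effects are APOE status, "baseline value of the outcome measure, baseline by visit-week interaction term, treatment group", visit, and the interaction of visit with treatment. On the covariance side, "the random effects will include site and subject. The within-subject covariance will be unstructured", followed by a list of fallbacks if the model does not converge. "The primary endpoint will be tested using model-adjusted least squares means at the week 72 visit".

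Concomitant medications: "FDA-approved monoclonal antibodies targeting brain amyloid are permitted, but participants must be stable for at least 6 months" before screening; Table 1, item 9, says the same. Table 1, item 2, admits both MCI and mild AD dementia.

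Randomization and blinding: in both phases "the randomization will be stratified by site". Allocation starts at 1:1:1 over two active doses and placebo, which is 2:1 active to placebo. It then becomes 1:2 until the arms are level, and 1:1 after that.

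Power calculation and sample size: the target difference of 0.7 CDR-SB points (SD 1.74) is described as "commensurate to the 35% to 40% amelioration of decline seen in the placebo arm" of a phase 2 donanemab trial.

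**The concern.** The protocol measures its own target against the effect of an anti-amyloid antibody, and it enrols people who take such antibodies alongside people who do not. Antibody use is therefore a plausible prognostic factor, possibly of a size similar to the target effect. Neither the stratification nor the model deals with it.

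APOE is in the model, but with one effect on change at every visit, while the baseline score has its own slope at each visit. If the APOE effect grows as the disease progresses, the model under-adjusts at week 72, where the test is made.

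The allocation ratio also changes during recruitment. A baseline factor whose prevalence moves over calendar time will then differ between arms systematically, not only by chance, and the listed model has no term for enrolment period.

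At stake are a little precision and, if prevalence drifts, a small bias.

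**Working it through.** **The plan's own figure.** Inputs from the power section: d = 0.38, drop-in 5%, dropout 20%, power 90% per endpoint; two-sided alpha of 5% from the analysis section. The diluted effect is 0.38 × 0.95 = 0.361. A t-based two-sample calculation gives 162.2 completers per arm, and 162.2/0.80 = 202.8, so 203. The other five rows of Table 3 also reproduce. With 203 × 0.80 = 162.4 completers per arm, the SE is √(2/162.4) = 0.111 SD, or 0.111 × 1.74 = 0.193 CDR-SB points, and power is 90.2%. The calculation takes no credit for covariates, so the omitted terms do not make it wrong.

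**Variance left in the residual.** The documents give neither the prevalence of antibody use nor its prognostic effect. Assume a shift of 0.38 × 1.74 = 0.66 points and prevalence p. The variance share is p(1−p) × 0.66²/1.74².

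| p (assumed) | Variance share | Equivalent participants (406 × share) | Power per endpoint if adjusted |
|---|---|---|---|
| 10% | 1.3% | 5 | 90.6% |
| 20% | 2.3% | 9 | 90.8% |
| 30% | 3.0% | 12 | 91.0% |

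**APOE by visit.** A repeated-measures simulation used 203 per arm, 20% dropout, three post-baseline visits, APOE prevalence 60%, antibody use 20%, and covariate effects that grow with visit to 0.2, 0.3 or 0.5 SD at week 72. Empirical SE of the week-72 contrast:

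| Model | 0.2 SD | 0.3 SD | 0.5 SD |
|---|---|---|---|
| APOE main effect only | 0.1088 | 0.1080 | 0.1074 |
| APOE by visit | 0.1088 | 0.1075 | 0.1064 |
| APOE by visit and antibody by visit | 0.1081 | 0.1067 | 0.1053 |

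APOE by visit alone lowers the SE by 0 to 0.9%. Both terms together lower it by 0.6 to 2%. The mean estimate is the same under every model to within about 0.001.

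**Drift under changing allocation.** Taking about 150, 150 and 106 participants in the three allocation stages, the active arm receives 100 + 50 + 53 = 203 and placebo 50 + 100 + 53 = 203. Stage 1 supplies 100/203 = 49.3% of active and 50/203 = 24.6% of placebo; stage 2 is the reverse; stage 3 is even. If use is 10% in stage 1 and 30% in stage 2 (assumption), the active-minus-placebo difference is 0.246 × (10 − 30) = −4.9 points. With an assumed antibody effect of 0.66 to 0.7 points, the bias is 0.049 × 0.66 to 0.7 = 0.03 points, and 0.0325/0.193 = 0.17 SE.

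The surplus of users falls in placebo, so the bias is toward the null. Power falls from 90.2% to about 87%, one-sided false-positive efficacy from 2.5% to 1.7%, and two-sided type I error is about 5.3%.

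**Price of an allocation-stage term.** Information on the treatment contrast is proportional to the sum of n₁n₂/(n₁+n₂) over stages. Without the term it is 203 × 203/406 = 101.5. With it, it is 100 × 50/150 + 50 × 100/150 + 53 × 53/106 = 93.2. The SE rises by √(101.5/93.2) = 1.044, and power by the planning formula goes from 90.2% to about 87.6%, before any variance that stage itself explains.

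**The case against.** The model is complete and prespecified, and choosing further covariates is partly a matter of preference. That stands, and it is why this is an improvement and not a defect.

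A reader might infer that known prognostic variation contaminates the treatment contrast. The documents do not support that. Within a fixed allocation ratio, an omitted baseline covariate stays in the residual and costs precision; it does not bias the estimate. Nor is the effect known. The 35–40% benchmark comes from a comparison of randomized arms in another trial, whereas users here have been stable on treatment for at least 6 months and were not randomized to it. On APOE, the Introduction reports a difference in treatment response in the pilot, not in prognosis.

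A reader might also picture a large chance imbalance. With 203 per arm, the SE of the between-arm difference in antibody use is 3.0, 4.0 or 4.5 points at 10%, 20% or 30% prevalence, so a 10-point gap is 3.4, 2.5 or 2.2 SE. Even that would move CDR-SB by only 0.07 points, or 0.36 SE, and the confidence interval already allows for chance variation of this kind.

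Disease stage is the weakest candidate. The baseline score, with its own slope at each visit, already carries most of it, and nothing in the documents puts a number on the remainder.

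The argument from drift survives these objections, because it does not depend on chance. It does depend on an assumed tripling of antibody use and an assumed effect size.

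**Conclusion.** The point holds as an optional improvement. The listed model omits baseline antibody use in a trial that admits users and does not stratify on it, and it fixes the APOE effect across visits while testing at week 72. The cost is about 0.6–2% of the SE, or under 1 point of power at an assumed 1–3% of variance.

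The changing allocation adds a possible bias of about 0.03 CDR-SB points. It works against benfotiamine if use rises and users decline less, and the other way if use falls. Prevalence, drift and prognostic effect are all assumptions. The documents do not support reading this as an invalid primary test, as inflated false-positive efficacy in the scenario shown, or as a wrong sample size.

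**What to change.** Add to the primary model baseline anti-amyloid antibody use (yes/no) with a visit interaction, and an APOE-by-visit interaction. Antibody status is established for eligibility and APOE is already a covariate. With three post-baseline visits and a two-level APOE factor (both assumed), this is 3 + 2 = 5 extra parameters for 406 participants. The model becomes slightly larger, but the section already lists convergence fallbacks.

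To deal with drift in any factor, add a term for allocation stage (2:1, 1:2, 1:1), preferably by visit for the same reason as APOE: 2 more parameters as a main effect, 6 by visit. This term is not free, since it raises the SE by about 4%, which is more than the covariates recover. If that price is too high for the primary model, the antibody term alone removes the part of the drift due to antibody use, and the stage-adjusted model can be prespecified as a sensitivity analysis. A disease-stage term is optional.

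The Trial status section describes recruitment as ongoing, so the wording can be settled before the efficacy data are unblinded.
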